### Intervention

The intervention is an employee staff health screening clinic available during usual work time (9 am–5 pm) and some evenings and weekends [37], administered by trained clinic nurses. It will last approximately 1 h and consist of two stages: (1) screening assessment for musculoskeletal, mental and cardiovascular health (which also includes lifestyle components such as alcohol consumption assessment), followed by (2) appropriate advice and/or referral of screen positives to appropriate services for management as per NHS/NICE recommendations (see Fig. 1 for overview) and personalised care pathways. There are 3 components to the screening intervention.

**Fig. 1 Fig1:**
[figure not shown]
Overview of NHS staff health screening check

#### Musculoskeletal health

We will use the Keele STarT back screening tool [48, 49] to categorise risk of future disability of low back pain and STarT MSK for non-back complaints [50, 51], and Orebro musculoskeletal pain screening questionnaire (short) — OMPSQ [52] — to enable comparison with international studies. Based on a model of stratified care, those with moderate scores on the STarT Back or STarT MSK tools will be referred to physiotherapy teams (according to local pathways), and those with high scores will receive enhanced physiotherapy including cognitive behavioural therapy to address associated psychological problems (Fig. 1).

#### Mental health

We will use the GAD7 [53, 54] (anxiety) and PHQ9 [54, 55] (depression) screening questionnaires to assess mental health. Participants without significant anxiety/depressive symptoms will be offered online mindfulness advice [56]. Those who are mildly/moderately affected will be advised to seek support from local counselling services such as Birmingham Healthy Minds [57] or, if severely affected, referred to their GP for immediate treatment (Fig. 1).

#### Cardiovascular health

Participants aged 40 years and over will receive the NHS Health Check [35]. This includes lifestyle checks (BMI (body mass index), exercise level (GPPAQ questionnaire [47]), smoking status and alcohol intake (alcohol use disorders identification test for consumption (AUDIT-C) questionnaire [58]), QRISK2 score [59]) and clinical measures (pulse, blood pressure, ECG, cholesterol, and HbA1C, eGFR and creatinine tests if appropriate). Actions will include referral to GP, weight management, smoking cessation and alcohol reduction services, as well as brief advice on exercise and diet according to UK recommendations (Fig. 1). The dementia awareness component for those over 65 will be excluded as there are few employees in this category. Participants aged under 40 years will be assessed for restricted lifestyle components of the NHS Health Check: BMI, exercise level, smoking status and alcohol intake, with the same advice applied and referrals to appropriate services. Blood samples will not be collected from participants aged under 40 years.

Participants reporting diagnosed conditions in any of the above 3 categories will not receive that element of the intervention. Results will be sent to participants’ GPs for their records if the participants provide consent.

#### Occupational health

All participants with an identified health condition will also be asked whether their condition is affected by/or affects their ability to work and what adjustments (if any) at work may improve their workability. If yes, they will be offered an optional referral to occupational health.

### Usual care

Participants in the control arm will receive usual access to medical services for management of any presenting condition (either through occupational health or their GP) and will remain eligible for the usual NHS Health Check via their GP.

### Outcomes

#### Primary outcomes and stop/go criteria

There are three co-primary outcomes:Recruitment (consented) as a proportion of those invitedDirect referral to any recommended services as a result of the three screening components (usually GP, physiotherapy, community psychological services depending on local pathways at the time of the study) (intervention arm only)Attendance at any recommended services (self-report at 26 weeks, intervention arm only)

These will inform criteria to progress to the definitive trial (Table 3).

**Table 3 Tab3:** Progression criteria informing decision about full trial

		Progression criteria		
	Description	Green (go)	Amber (pause)	Red (stop)
Recruitment^a^	% of invited employees consenting to take part	> 25%	15–25%	< 15%
Referred directly to a service^b^	% of participants randomised to intervention arm referred to specified services Measured at 26 weeks	> 30%	10–30%	< 10%
Attendance at referrals^c^*	% of referrals which resulted in self-reported attendance at the service at least once. Measured at 26 weeks	> 50%	30–50%	< 30%
**Action**		**If ALL criteria are GREEN, proceed to full trial with protocol unchanged**	**If ANY of these criteria are AMBER, adapt protocol appropriately using information from the process evaluation before proceeding to full trial**	**If ALL of these criteria are RED, consider whether current protocol is not feasible** **If ONE OR TWO of these criteria are RED, consider whether adaptations are needed**

^a^A recent study of low-paid government workers receiving an NHS Health Check in the workplace demonstrated benefits to cardiovascular health with 20% uptake of the intervention [60] and experience from a primary care COPD screening trial with > 35% uptake [61] and primary care cohort with > 25% uptake [62]. ^b^A feasibility study of a cardiovascular health check in an NHS hospital showed that 33% required follow-up with a GP or other health professionals [63]; experience from our pilot clinic with cardiovascular and mental health checks showed that 35% required further follow-up. ^c^The feasibility study mentioned above also showed that 54% of those referred to further services had attended within 5 weeks, and most of the remainder intended to do so [63]. *We will present both % of referred participants attending at least one of their referrals (at least once) and % of total referrals resulting in an attendance

#### Secondary outcomes

Baseline characteristics of included participants and hospital population for comparisonDescription of the results of the intervention screening assessmentsNumber and type of direct referrals to recommended services (intervention arm only)Attendance at each individual recommended service (self-report at 26 weeks; intervention arm only)Lifestyle relevant to screening intervention advice and referrals (self-report at 26 weeks compared with baseline):Physical activity index measuring exercise levels (GPPAQ) [47]Smoking statusWeight (kg)Acceptability of intervention to participants and health screening clinic staff (interviews)Feasibility of trial processes (completeness of relevant data items, interviews)Indication of contamination (comparing pre/post data for health behaviours and healthcare/other service utilisation in control arm)

#### Outcomes related to the definitive trial

Absenteeism at 26 weeks with reasons, measured by days and spells, is as follows:Self-report absolute absenteeism, relative absenteeism and relative hours of work — for the last 7 days and last 28 days (WHO-HPQ) [45] at 26 weeksSelf-report absenteeism 6-month recall period at 26 weeksEmployee records of absenteeism at 26 weeks, which will be the primary outcome of the definitive trial, using routine collected data from the NHS Electronic Staff Record Programme, linked to employee ID and provided directly by electronic HR recordsPresenteeism at 26 weeks (self-report absolute presenteeism and relative presenteeism for the last 28 days (WHO-HPQ)) [45]Attendance at occupational health service (self-report at 26 weeks)Healthcare utilisation (self-report at 26 weeks (e.g. GP consultations, hospital admissions))EQ-5D-5L index value measuring health-related quality of life (EuroQol EQ-5D 5-level) [46] at 26 weeksPatient (self-report questionnaire) and trial intervention resource use/costsScreening assessment duration and resources used

### Process evaluation

A mixed-methods process evaluation will explore programme reach; fidelity of screening delivery; attendance at referrals; participants’ views of the intervention; views and experiences of the training received by those delivering the intervention, its acceptability and satisfaction with the intervention overall; and views of providers of follow-on services, e.g. GPs and “healthy minds”. In addition, we will explore the views of potential beneficiaries, e.g. other NHS organisations who might be willing to run the trial such as ambulance services and GP groups and private, non-healthcare organisations who might be interested in delivering and evaluating such a service for their setting.

Quantitative data to support the process evaluation will be obtained from the following:*Recruitment and follow-up data*, e.g. response rate; proportions of those invited consenting, being randomised and attending the screening; follow-up at 26 weeks*Baseline questionnaire* to assess characteristics, e.g. data on age, ethnicity, marital status, Index of Multiple Deprivation, educational attainment and employment role of the employees recruited to study (programme reach)*Logs* kept by the staff health screening programme recording attendance, screening tests undertaken and duration of contacts (fidelity)*Healthcare issues* identified at the employee screening and referrals made to GP and other services (fidelity)*Self-report of attendance at recommended services* from follow-up questionnaires (uptake)*Brief questionnaire to staff* not taking up the offer of the study to ascertain reasons for not participating and a question to participants to ascertain which recruitment method most prompted them to participate (reach)

Focused qualitative interviews lasting approximately 30 min either face to face, by voice over Internet protocol (e.g. zoom) or telephone according to participant preference will be conducted with the following:Up to 40 participants, sampled on age, gender and ethnicity, occupation, site, shift pattern and department, selected from those randomised.

Those in the intervention group are as follows:A.Did not attend screeningB.Did not need referral to other servicesC.Needed referral to other services

We will explore acceptability, barriers and facilitators to the intervention, views on the benefits of the intervention, their experience of it, its value, disbenefits, fears about confidentiality of workplace service, views on occupational health services and their experience of being referred to other services.D.The usual care group﻿: to explore awareness of the trial and its intervention and if prompted to seek a health check outside of the trialStaff undertaking health checks: exploring the feasibility of implementing the intervention in theory/practice, training and their experiences of delivery in relation to the different cadres of staffUp to 12 GPs and staff delivering relevant services exploring their experience of receiving referrals, the acceptability of the process and availability of appropriate referral pathways from primary care, e.g. smoking cessation and physiotherapy servicesUp to 10 potential beneficiaries (e.g. ambulance service or private sector companies) exploring the feasibility and acceptability of conducting the trial and/or delivering the intervention in other contexts.

### Sample size

The study is not designed or powered to detect a statistically significant difference in efficacy between the two trial arms. We aim to recruit 480 participants (20 per week) in 24 weeks. With this sample size, the 95% confidence interval (CI) for the proportion of staff recruited can be estimated to be 4% either side of the estimate (e.g. for a 25% recruitment rate, the 95% CI will lie between 21 and 29%).

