### Allocation to trial arm

On completion of the baseline questionnaire, clinic staff will receive an alert to check eligibility criteria and consent, and participants will then be randomised to intervention or control arm. Randomisation will be at the level of the individual in a 1:1 ratio, using a minimisation algorithm to ensure balance on the following variables: age, sex, self-reported job categories, nightshift work and centre. To avoid predictability, a “random element” will be included in the minimisation algorithm. Given the nature of the intervention, blinding will not be possible.

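### The ±4-point precision given for the recruitment proportion puts the 480 recruits in the denominator, where the number of staff invited belongs; the correct figure is about ±2 points, and the stated one does not justify 480

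*Protocol article*

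**What the plan says.** The Sample size section of the protocol article opens by ruling out a power calculation: "The study is not designed or powered to detect a statistically significant difference in efficacy between the two trial arms". It then sets the target: "We aim to recruit 480 participants (20 per week) in 24 weeks". The next sentence, beginning "With this sample size", says that "the 95% confidence interval (CI) for the proportion of staff recruited can be estimated to be 4% either side of the estimate", and gives the example that "for a 25% recruitment rate, the 95% CI will lie between 21 and 29" per cent. No other quantitative reason for 480 is given.

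The outcome itself is defined under Primary outcomes and stop/go criteria. The list of co-primary outcomes takes those who consent over those invited. Table 3 repeats this as the percentage "of invited employees consenting to take part", with green above 25%, amber from 15 to 25% and red below 15%. The article gives no expected number of invitations.

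**The concern.** The precision of a proportion is governed by its denominator, which here is the number of staff invited. The 480 in the Sample size section is the number who join, so it is the numerator. The interval appears to have been computed as if 480 people were invited and a quarter of them joined, which would yield 120 participants and contradict the target.

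What is at stake is the justification of the sample size. The sentence is the only numerical support for 480, and it describes a precision that the design does not have. A colleague using it to plan invitations, or to judge whether 480 is reasonable, would be working from a wrong figure.

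**Working it through.** **Inputs**
- Target recruited: 480 (Sample size; 20 × 24 = 480).
- Example rate: 25%, interval 21 to 29% (Sample size).
- Recruitment = consented / invited (co-primary outcome list and Table 3).
- Allocation: "Randomisation will be at the level of the individual in a 1:1 ratio" (Allocation to trial arm), so about 240 per arm.
- Number invited: not stated. It is derived below as 480 / rate.

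The formula throughout is half-width = 1.96 × √(p(1 − p)/n).

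**1. Reproducing the printed interval**

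p = 0.25, n = 480: 1.96 × √(0.25 × 0.75/480) = 3.87 points, giving 21.1 to 28.9%. The Wilson interval is 21.3 to 29.1% and the exact interval 21.2 to 29.1%. All three round to the printed 21 to 29%, so 480 was used as the denominator.

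**2. Using the defined denominator**

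480/0.25 = 1,920 invited. 1.96 × √(0.25 × 0.75/1,920) = 1.94 points, giving 23.1 to 26.9% (Wilson and exact: 23.1 to 27.0%).

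Other rates, always with 480 recruits:

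| Recruitment rate | Implied number invited | 95% half-width (points) |
|---|---|---|
| 15% | 3,200 | 1.24 |
| 20% | 2,400 | 1.60 |
| 25% | 1,920 | 1.94 |
| 30% | 1,600 | 2.25 |
| 35% | 1,371 | 2.52 |

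**3. Whether any reading gives ±4 points**
- With n = 480/p, the half-width is 1.96 × √(p²(1 − p)/480). This is largest at p = 2/3, where it is 3.44 points. No recruitment rate reaches 4.
- If 480 were the number invited, a 25% rate would give 480 × 0.25 = 120 participants, not 480.
- Inflating 1.94 to 4 points would need a design effect of about (4/1.94)² ≈ 4.3. None is stated.
- Table 1 lists 9,000 + 11,000 + 6,000 + 3,000 = 29,000 staff. A finite-population correction on that total narrows the interval to ±1.87 points.

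**4. What ±4 points would require**

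n = 1.96² × 0.25 × 0.75/0.04² ≈ 450 invited. At 25% that is 450 × 0.25 ≈ 113 recruits.

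**5. Outcomes whose precision does depend on 480**
- Referral, intervention arm: p = 0.30, n = 240: 1.96 × √(0.30 × 0.70/240) = 5.80 points.
- Attendance at recommended services: the denominator is not known in advance. Assume 30% of 240 = 72 referred participants, all followed up. At p = 0.50: 1.96 × √(0.25/72) = 11.5 points. If 10% were referred (24 people, the red/amber boundary in Table 3) this becomes 1.96 × √(0.25/24) = 20.0 points. If 35% were referred (84 people, the pilot clinic figure in the Table 3 footnote) it becomes 1.96 × √(0.25/84) = 10.7 points.

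**The case against.** The strongest reply is that the error is harmless. Recruitment will be estimated about twice as precisely as claimed. The Statistical methods section reports the primary outcomes as observed proportions with 95% CIs, and those will rest on the actual number invited. No threshold, estimate or decision uses the ±4 points. All of this stands, and it limits the seriousness of the point. It does not make the printed figure right.

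A second reply is that the article condenses a fuller protocol (version 5.0), so the lack of precision figures for referral and attendance is not in itself an error. That also stands. Those figures are needed only because, once the recruitment interval is corrected, nothing else in the section supports 480.

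A reader might infer that all three progression criteria rest on about ±4 points, or that the text conceals weaker precision elsewhere. The document does not support either reading: its claim is confined to the proportion of staff recruited.

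A reader might also want to attach misclassification rates to the attendance criterion. These would rest on an assumed number of referred participants, whereas Table 3 scores attendance per referral and its footnote promises both counts. One person may have several referrals, which raises the count and correlates the observations; non-response at 26 weeks lowers it. The attendance half-width is therefore an illustration under a labelled assumption.

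**Conclusion.** The stated precision is wrong as written. At a 25% recruitment rate with 480 recruits, the 95% CI is about 23 to 27% (±1.94 points), not 21 to 29%. The figure of about 1,920 invited is derived from the protocol's own 480 and 25%. The conclusion does not hinge on that rate, because no rate with 480 recruits gives ±4 points. Since ±4 points at 25% would take only about 113 recruits, the sentence does not justify 480.

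It does not follow that 480 is too few or that the recruitment criterion is unsafe: for recruitment the mistake errs on the cautious side. Nor does it follow that Table 3 needs a new rule, such as giving the lower colour to a criterion whose CI crosses a boundary. That would move every progression threshold and would answer no error in the document. The point is a correction to the sample size statement, with no bearing on the validity of the trial's conclusions.

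**What to change.** Replace the precision sentence in the Sample size section and leave 480, Table 3 and the analyses as they are. Suggested content:

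- With 480 recruits at a 25% recruitment rate, about 1,920 staff will have been invited and the 95% CI will be about 23 to 27%. The half-width is about 1.2 points at 15% (3,200 invited) and 2.5 points at 35% (1,371 invited).
- The target of 480 is supported by the intervention-arm outcomes. With about 240 in that arm, a 30% referral rate has a 95% CI of about ±6 points.
- Assuming about 72 referred participants with full follow-up, 50% attendance has a 95% CI of about ±12 points. State that Table 3 counts referrals, so the denominator may differ.

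The cost is a few sentences. The article would then show openly that attendance is estimated much less precisely than recruitment, which the sponsor should be content to defend for a pilot.

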### Analyses

#### Statistical methods

The primary comparison groups will be composed of those randomised to the health screening clinic arm (intervention) and those randomised to the usual care arm (control). All analyses will use the intention to treat principle, i.e. participants will be analysed in the treatment group to which they were randomised, irrespective of adherence or other protocol deviation.

Analyses of feasibility, absenteeism, presenteeism and clinical outcomes will take the form of simple descriptive statistics (e.g. proportions and percentages, means and standard deviations). The primary outcomes will be presented descriptively as proportions with 95% confidence intervals.

Secondary outcomes will be presented descriptively as proportions for categorical data and means and standard deviations/medians and interquartile ranges for continuous data, along with 95% confidence intervals. No formal statistical analysis will be undertaken.

Due to the electronic system of collecting data, it is anticipated that missing data will be minimal. The main analysis will use available data online; however, the amount of missing data will be assessed in order to inform decision regarding data collection for the definitive trial.

#### Qualitative analysis

Interviews and focus groups will be audio-recorded and transcribed clean verbatim for analysis. A thematic analysis of content will be informed by the Framework analytical approach [64]. Analysis and discussion will include the experienced qualitative team in partnership with the patient and public involvement (PPI) group to provide multiple perspectives on the data. Data collection and analysis will run concurrently so that emergent analytical themes can inform further data collection.

### Health economic analysi**s**

To inform the design of a full economic evaluation, we will conduct a descriptive cost-consequence analysis presenting disaggregated information on all relevant resource use and outcomes for both trial arms and costs of screening. Resource use, absenteeism, productivity loss data and the completeness of the data will be assessed. Resource use required for screening will be multiplied by unit costs obtained from standard sources (NHS Reference Costs, Unit Costs of Health and Social Care) and healthcare providers. Responses to the EQ-5D 5L questionnaire, valued using the crosswalk algorithm, will be used to calculate quality-adjusted life years (QALYs) using the area under the curve method. Analyses will be mainly descriptive, and all costs and outcomes will be summarised using means and 95% confidence intervals.

### Current status of trial and impact of COVID-19 pandemic

Current status is as follows: At submission this trial was still under recruitment. Ethical approval for the trial was obtained in March 2020, but was not able to proceed due to the COVID-19 pandemic. Two hospital sites granted permission to commence the trial in December 2020, but after a very short period, recruitment was paused again due to a spike in COVID-19 cases. The trial recommenced in May 2021 in all four sites. A 6-month extension to the trial was been awarded from the funder until October 2021.

### Patient and public involvement (PPI)

The study design has been informed by a survey of 60 QEHB staff and meetings with patients, relatives, friends accompanying them, members of the public, UHB’s hospital executive board, senior/middle managers, local GPs, the University of Birmingham’s patient advisory group, staff consultations relating to a self-referral staff health screening clinic at QEHB, data from the annual NHS staff survey at QEHB (*n* = 3381 (35%) response) and a PPI group specifically set up to inform eTHOS throughout the trial, comprising 4–6 staff members and patients.

